#### Allocation concealment

The serial number assigned to each patient will be placed in an opaque sealed envelope in the custody of a person not involved in the specific study to ensure concealment.

### Blinding

Member of the research team who enters the information is the only ones who know about the participants’ allocation. The data collectors, random allocation program makers, data analysts, and outcome evaluators are blinded to group allocation. And the participants are similarly blinded to their own group allocation. Participants are similarly blinded to their own group allocation and they will be told not to share their positive event records with others. Results from the outcome measures will not be revealed to the participants until after all recruitment, treatment, and assessments have been performed for all 80 participants.

### Procedures

#### Recruitment

Participants will be recruited from The First Affiliated Hospital of Soochow University located in Suzhou, China. This institution will advertise the trial by posting recruitment posters on the hospital website or bulletin board.

#### Study schedule

The items to be measured at each visit are listed in Table 1.

**Table 1 Tab1:** Schedule of enrollment, intervention, and assessment

Items	Screening	Post-allocation							3 months after the trial
	Visit 1 (day − 7 to − 2)	Visit 2 (day 0)	Visit 3 (week 1)	Visit 4 (week 2)	Visit 5 (week 3)	Visit 6 (week 4)	Visit 7 (week 8)	Visit 8 (week 12)	Visit 9 (week 24)
Informed consent	X								
Inclusion/exclusion criteria	X								
Randomization		X							
Intervention		X	X	X	X	X	X	X	
Basic information^a^	X								
Body measurement^b^	X	X	X	X	X	X	X	X	X
Vital signs	X	X	X	X	X	X	X	X	X
Medical history^c^	X								
General physical examination	X							X	X
Compliance monitoring				X					
Healthy behaviors	X							X	X
Readmission rate								X	X
Anxiety	X							X	X
Psychological capital	X							X	X
Subjective well-being	X							X	X
Clinical indicators^d^	X							X	X
Adverse event monitoring			X	X	X	X	X	X	X

^a^Age, gender, job, medical insurance, exercise, smoking habit, drinking habit, sleep pattern, etc.

^b^Height and weight, but only weight for visit 2 and follow-up

^c^Including general medical history and family history of CHD

^d^Including TG, TC, LDL, HDL, blood glucose, etc.

#### Baseline assessment

After the screening visit, if a participant fulfills the inclusion criteria and has signed the informed consent form, he will be assigned to the baseline assessment. The baseline assessment takes place at visit 1. Baseline assessment includes patients’ basic information (such as age, gender, education, income, occupation, medical insurance, comorbidity, exercise, smoking habit, drinking habit, sleep pattern, etc.), body measurement (height, body weight, body mass index (BMI), blood pressure (BP), heart rate, etc.), clinical indicators (TG, TC, LDL, and blood glucose, etc.), and questionnaires (Health Promotion Lifestyle Scale II (HPLP II), Self-rating Anxiety Scale (SAS), Positive Psychological Capital Questionnaire, General Well-Being Scale).

#### Intervention

After randomization, the patients in the control group will receive conventional nursing, and the patients in the intervention group will record positive events for 3 months in addition to conventional nursing, that is, once a week for 12 weeks. Each patient in the intervention group will be assigned a notebook to record positive events and a health education manual. The specific implementation plan is as follows.

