#### Intervention group

On the basis of the same conventional nursing as the control group, the following measures were given:

Develop positive psychological intervention programs: the intervention plan was designed by our team based on the positive psychology intervention program by Seligman [22] and also based on a review of literature and expert consultation [27–29]. Related literature reported that the period of positive psychological intervention is generally more than 8 weeks [30]. Lan [19] conducted a 10-week intervention on type 2 diabetes patients, and their depression and anxiety psychology was also effectively improved, and their self-care ability was improved too. So, the implementation time of positive event recording in this study is planned to be 3 months, and the specific implementation methods, time, and measures are shown in Table 2.

**Table 2 Tab2:** Intervention program for recording positive events in patients after PCI

Week	Intervention forms	Intervention theme	Measures
1	Face-to-face	Three positive events	Review 3 events about your positive state this week and record them (for example, I finished my exercise today, and I took medicine under the doctor’s advice today etc. It has nothing to do with the size of the matter). Once in a week
2	Online	Personal strengths	Conduct a brief assessment of your strengths, recording the strengths, as well as the practice and results. Once in a week
3	Online	Expressing gratitude	Recall the help you have received in your life, record it, and write a letter of thanks to the person. Once in a week
4	Online	Enjoyable and meaningful activities	Complete 3 enjoyable and meaningful activities on your own and keep records. Once in a week
5	Online	Experiencing success	Review previous successes, learn to enjoy them, summarize the reasons for success, and record. Three times in 1 week
6	Online	Acts of kindness	Complete three acts of kindness and record the pleasant experiences associated with them. Once in a week
7	Online	Eliminating negativity	Eliminate negativity (When there are negative emotions, record one thing that makes you happy). Three times in 1 week
8	Online	Interests and habits	Develop your own interests and hobbies, and summarize and record happy experiences related to them. Once in a week
9	Online	Accomplishing the goal	Set realistic goals and achieve them, and record the fulfilling, pleasant feelings associated with them. Once in a week

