10	Online	Summarizing life	Summarize your past great life and look to the future, write down 1 − 2 pages. Once in a week
11–12	Online	Repeat training	For the next 2 weeks, repeat the above and write it downIntervention implementation: using a combination of face-to-face intervention, telephone, or WeChat remote intervention. Patient recruitment and week 1 intervention instructions were completed during the patient’s hospitalization, and the researchers communicated with the patients face to face, distributed the intervention instruction manual, explained the 12-week intervention plan and matters needing attention in the exercise process, and assigned the tasks in the first week. Thereafter, the researcher will communicate with participants online (via phone or WeChat) for approximately 20 − 30 min each week. During each communication session, the researcher reviewed the patient’s recordings for the previous week, learned about the patient’s thoughts and feelings during the intervention and gave feedback, and introduced the schedule for the following week. The specific implementation is provided in Table 2.Follow-up: mainly by phone or WeChat, once a week in the first month after discharge and once a month after that until 3 months. Follow-up (via phone or WeChat) will continue for 3 months after the end of the intervention, with a frequency of 3 months. Each follow-up time is about 5 − 10 min. If the patient has any questions, the time can be extended as appropriate.Recording log: each individual is given a recording log and asked to record the number and time of recording every day. The data will be used to assess intervention compliance.

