#### Control group

Conventional nursing: on the first day after enrollment, researchers communicate with patients one-on-one and explain CHD-related knowledge to patients, including risk factors, diet strategies, weight control, physical exercise, blood pressure and lipid management, etc. At the time of discharge, the charge nurse stresses the importance of medication, regular checkups, smoking cessation, exercise, and a healthy diet to the patient and distributes a health management manual for patients with coronary heart disease (The main contents of this manual include the operation process of coronary intervention, knowledge of medication, importance of review, diet management, exercise mode, and so on.).Follow-up by phone or WeChat: the investigator focuses on understanding the patient’s recovery and giving health instructions. Frequency and duration of follow-up visits: once a week in the first month after discharge and once a month after that until 3 months. Follow-up will continue for 3 months after the trial at a frequency of 3 months. Each follow-up lasts about 5 − 10 min, during which patients can be consulted by phone or WeChat. It is not difficult to extend the time appropriately.

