### Outcome

The primary outcome indicators are healthy behaviors, readmission rate, and anxiety level, and the secondary outcome indicators are psychological capital, subjective well-being, and clinical indicators (including TC, LDL, HDL, blood glucose, body mass index, etc.).

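### A health education manual is listed for the intervention arm only, on top of conventional nursing that is said to be the same in both arms and already includes a health manual

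*Protocol article*

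**What the plan says.** Four statements in the protocol article bear on what printed material each arm receives.

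- **Intervention section, background care:** "the patients in the intervention group will record positive events for 3 months in addition to conventional nursing".
- **Intervention section, next sentence:** "Each patient in the intervention group will be assigned a notebook to record positive events and a health education manual". No content is given for this manual, and the only timing is that it follows randomization.
- **Intervention group section:** the programme is introduced with "On the basis of the same conventional nursing as the control group, the following measures were given". The delivery text after Table 2 says that, during the hospital stay, the researchers "distributed the intervention instruction manual, explained the 12-week intervention plan".
- **Control group section, which defines conventional nursing:** "on the first day after enrollment, researchers communicate with patients one-on-one and explain CHD-related knowledge to patients". At discharge the charge nurse gives advice and "distributes a health management manual for patients with coronary heart disease". The listed contents include "knowledge of medication, importance of review, diet management, exercise mode, and so on". Follow-up calls with health instructions come after that.

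On outcomes, the Outcome section states: "The primary outcome indicators are healthy behaviors, readmission rate, and anxiety level". Healthy behavior is measured by HPLP II at screening, week 12 and week 24.

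**The concern.** The trial is an add-on comparison: conventional nursing plus recording against conventional nursing alone. A difference can be credited to recording only if everything else with a bearing on the outcome is the same in both arms. Education on diet, exercise and medication bears directly on a healthy-lifestyle score. If one arm receives an additional health education document, part of any HPLP II difference could come from that document.

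No analysis could separate the two. The manual would go to every intervention patient and to no control, so its effect would be completely confounded with allocation. The only remedy lies in what is handed out.

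**Working it through.** No figure in the plan is at issue. The check is to set the statements side by side and ask what each arm receives under each possible identity of the manuals.

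**Inputs**

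| Item | Where stated | Arm | Time | Content |
|---|---|---|---|---|
| Health education manual | Intervention | Intervention only | After randomization, not otherwise stated | Not described |
| Intervention instruction manual | Intervention group, delivery text | Intervention only | In hospital, with the first-week instructions | Handed out when the 12-week plan is explained |
| Health management manual | Control group, conventional nursing | Both, since conventional nursing is stated to be the same | Discharge | PCI procedure, medication, review, diet, exercise |

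**Step 1. Conventional nursing.** The Intervention and Intervention group sections both say that recording is added to conventional nursing, and the latter says it is the same nursing as in the control arm. Intervention patients therefore also receive the one-on-one teaching, the discharge advice, the discharge manual and the follow-up calls. Each arm has at least one health manual.

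**Step 2. The possible identities of the health education manual.** The notebook is not counted.

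| Reading | Manuals, intervention | Manuals, control | Consequence |
|---|---|---|---|
| A. A separate, third document | 3 | 1 | One extra health education document in one arm: 40 of 40 against 0 of 40 patients |
| B. The discharge manual under another name | 2 | 1 | Health education is equal; the Intervention section wrongly lists a shared item as belonging to one arm |
| C. The instruction manual under another name | 2 | 1 | The only extra item is the programme manual; its title suggests health education and its content is not stated |

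**Step 3. Which reading the text favors.** The sentence is restricted to the intervention group, pairs the manual with the notebook, which is an intervention-only item, and directly follows the statement that recording is added to conventional nursing. Taken literally, that is reading A. Nothing in the article excludes B or C.

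**Step 4. Size.** The article gives no effect of a manual on HPLP II and no content for this one, so no bias can be calculated. Under reading A, the relevant quantity is the increment over individual teaching, discharge counselling, a discharge manual and follow-up calls, all of which both arms receive. That increment is probably small.

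**The case against.** The strongest reply is that the text states equal background care and that three titles in a condensed article may be loose wording. Both arms receive lifestyle education from the first day after enrollment, so one more booklet would be a minor addition. An inventory of printed material is also commonly left to the full protocol.

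Much of this stands. It disposes of several stronger readings that a reader might infer:

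- **That the arms are shown to receive unequal lifestyle education.** They are not. The manual's content is undescribed, and the count of 40 against 0 holds only if it is a separate document.
- **That each arm has its own manual, one set against the other.** The discharge manual belongs to conventional nursing, which both arms receive.
- **That the intervention arm gets its manual at allocation, or earlier than controls.** The word assigned in the Intervention section means given. In-hospital delivery is stated only for the instruction manual, and that timing carries over only if the two are the same document.
- **That intervention material should contain nothing on exercise or medication.** The first-week examples in Table 2 are finishing one's exercise and taking medicine as advised, so such a ban would conflict with the programme itself.

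The reply does not remove the point. Equal conventional nursing is exactly what makes a further item for one arm an addition. Nor is this a detail left to another document: the article does state what the intervention group receives. Under every reading, the sentence in the Intervention section needs correction or clarification.

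**Conclusion.** The point holds in a limited form. On its literal wording, the protocol gives the intervention arm one more health education document than control. This is a possible co-intervention on healthy behaviors, one of three primary outcomes. If the manual is in fact one of the other two, the fault is in the listing or the naming, and the sections must be reconciled.

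The conclusion rests on two assumptions: that the statement of identical conventional nursing is meant as written, and that a health education manual has lifestyle content, which is inferred from its title alone. The size of any bias cannot be derived from the document and is probably small given the education that both arms receive. The correction is still worth making because it is cheap and no later analysis could separate an extra manual from recording.

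**What to change.** Reconcile the Intervention, Intervention group and Control group sections as follows:

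1. Move the CHD health education manual into the definition of conventional nursing. Give the identical manual to every patient in both arms at the same time point.
2. Limit intervention-only material to the notebook and the instructions for recording positive events. The Table 2 examples can remain.
3. Use one name for each document throughout.
4. Document which manuals the participants already enrolled received, by arm. Trial status reports 20 recruited at the time of writing. If recruitment has since ended, this step and a clear statement in the trial report are what remain.

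Cost: changes of wording and at most 40 extra booklets, one for each of the 40 control patients, and none if the manual is already the shared one. No additional visits or staff are needed.

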#### Intervention group

On the basis of the same conventional nursing as the control group, the following measures were given:

Develop positive psychological intervention programs: the intervention plan was designed by our team based on the positive psychology intervention program by Seligman [22] and also based on a review of literature and expert consultation [27–29]. Related literature reported that the period of positive psychological intervention is generally more than 8 weeks [30]. Lan [19] conducted a 10-week intervention on type 2 diabetes patients, and their depression and anxiety psychology was also effectively improved, and their self-care ability was improved too. So, the implementation time of positive event recording in this study is planned to be 3 months, and the specific implementation methods, time, and measures are shown in Table 2.

**Table 2 Tab2:** Intervention program for recording positive events in patients after PCI

Week	Intervention forms	Intervention theme	Measures
1	Face-to-face	Three positive events	Review 3 events about your positive state this week and record them (for example, I finished my exercise today, and I took medicine under the doctor’s advice today etc. It has nothing to do with the size of the matter). Once in a week
2	Online	Personal strengths	Conduct a brief assessment of your strengths, recording the strengths, as well as the practice and results. Once in a week
3	Online	Expressing gratitude	Recall the help you have received in your life, record it, and write a letter of thanks to the person. Once in a week
4	Online	Enjoyable and meaningful activities	Complete 3 enjoyable and meaningful activities on your own and keep records. Once in a week
5	Online	Experiencing success	Review previous successes, learn to enjoy them, summarize the reasons for success, and record. Three times in 1 week
6	Online	Acts of kindness	Complete three acts of kindness and record the pleasant experiences associated with them. Once in a week
7	Online	Eliminating negativity	Eliminate negativity (When there are negative emotions, record one thing that makes you happy). Three times in 1 week
8	Online	Interests and habits	Develop your own interests and hobbies, and summarize and record happy experiences related to them. Once in a week
9	Online	Accomplishing the goal	Set realistic goals and achieve them, and record the fulfilling, pleasant feelings associated with them. Once in a week
10	Online	Summarizing life	Summarize your past great life and look to the future, write down 1 − 2 pages. Once in a week
11–12	Online	Repeat training	For the next 2 weeks, repeat the above and write it downIntervention implementation: using a combination of face-to-face intervention, telephone, or WeChat remote intervention. Patient recruitment and week 1 intervention instructions were completed during the patient’s hospitalization, and the researchers communicated with the patients face to face, distributed the intervention instruction manual, explained the 12-week intervention plan and matters needing attention in the exercise process, and assigned the tasks in the first week. Thereafter, the researcher will communicate with participants online (via phone or WeChat) for approximately 20 − 30 min each week. During each communication session, the researcher reviewed the patient’s recordings for the previous week, learned about the patient’s thoughts and feelings during the intervention and gave feedback, and introduced the schedule for the following week. The specific implementation is provided in Table 2.Follow-up: mainly by phone or WeChat, once a week in the first month after discharge and once a month after that until 3 months. Follow-up (via phone or WeChat) will continue for 3 months after the end of the intervention, with a frequency of 3 months. Each follow-up time is about 5 − 10 min. If the patient has any questions, the time can be extended as appropriate.Recording log: each individual is given a recording log and asked to record the number and time of recording every day. The data will be used to assess intervention compliance.

#### Control group

Conventional nursing: on the first day after enrollment, researchers communicate with patients one-on-one and explain CHD-related knowledge to patients, including risk factors, diet strategies, weight control, physical exercise, blood pressure and lipid management, etc. At the time of discharge, the charge nurse stresses the importance of medication, regular checkups, smoking cessation, exercise, and a healthy diet to the patient and distributes a health management manual for patients with coronary heart disease (The main contents of this manual include the operation process of coronary intervention, knowledge of medication, importance of review, diet management, exercise mode, and so on.).Follow-up by phone or WeChat: the investigator focuses on understanding the patient’s recovery and giving health instructions. Frequency and duration of follow-up visits: once a week in the first month after discharge and once a month after that until 3 months. Follow-up will continue for 3 months after the trial at a frequency of 3 months. Each follow-up lasts about 5 − 10 min, during which patients can be consulted by phone or WeChat. It is not difficult to extend the time appropriately.

### Outcome

The primary outcome indicators are healthy behaviors, readmission rate, and anxiety level, and the secondary outcome indicators are psychological capital, subjective well-being, and clinical indicators (including TC, LDL, HDL, blood glucose, body mass index, etc.).

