### Objectives

The general aim of this study is to evaluate the efficacy of positive event recording in patients after PCI.

The primary objective is to explore whether recording positive events will promote or maintain healthy behaviors, reduce readmission rate, and improve anxiety of patients after PCI.

The secondary objective is to explore whether recording positive events can promote the positive emotions, subjective well-being, and clinical laboratory indicators (such as total cholesterol (TC), triglyceride (TG), high-density lipoprotein (HDL), low-density lipoprotein (LDL), height and weight, etc.) of patients after PCI.

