#### Primary outcome measure

Healthy behavior: The Health Promotion Lifestyle Profile II (HPLP II) will be used to measure patient’s healthy behavior. The scale was revised by American nursing scientist Walker [31], which mainly includes 6 dimensions and 52 items. The total Cronbach’s *α* coefficient of the scale is 0.94, and the Cronbach’s *α* number of each dimension is 0.79–0.87. Each item is scored by grades 1–4; the higher the score, the better the healthful lifestyle. It will be checked at visits 1, 8, and 9.Readmission rate: In this study, readmission is defined as the readmission caused by cardiovascular problems, including hypertension, angina, arrhythmia, cardiac insufficiency, etc., excluding the cases of readmission due to cold, tumor, and other factors. The readmission will be followed up by telephone for 3 months. The readmission information will be collected at visits 8 and 9.Anxiety: The Self-rating Anxiety Scale (SAS) will be used to measure the anxiety of patients with CHD. The scale was compiled by Chinese professor Zung (1971), there are 20 items on the scale, each item is scored by grades 1–4, and items 5, 9, 13, 17, and 19 are scored in reverse. According to the results of Chinese norm model results [32], the cut-off value of the SAS standard score is 50, of which 50–59 is mild anxiety, 60–69 is moderate anxiety, and over 69 is severe anxiety. The scale has been widely used in China and its validity and reliability have been verified (Cronbach’s *α* 0.82). The anxiety score will be measured at visits 1, 8, and 9.

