#### Sample size calculation

Calculated according to the formula of sample size estimation based on the comparison of the mean of two independent samples [35]: *n*_1_ = *n*_2_ = 2[(*Z*_*α*_ + *Z*_*β*_)*σ*/*δ*]^2^ + *Z*^2^_α_, *σ* is the standard deviation, *δ* is the difference between the two population means, *n*_1_ and *n*_2_ are the required contents of the two samples, respectively, and *Z*_*α*_ and *Z*_*β*_ are *Z* values corresponding to the type I error probability and the type II error probability, respectively. At bilateral *α* = 0.05, power = 0.8, *Z*_*α*/2, ν_ = 1.96, *Z*_*β, ν*_ = 0.842, *σ* = 12.68, and *δ* = 10.39, the sample size for each group is 25 cases. Considering the 20% sample loss rate and other factors, the total number of samples is expected to be 80.

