### Statistical analysis

The Kolmogorov–Smirnov test will be used to test the normal distribution of continuous variables. Continuous variables will be presented by mean ± standard deviation (SD) if they are normally distributed or by median with interquartile range if they are not normally distributed. For the comparison of measurement data between the two groups, a *t*-test of two independent samples will be used for normal distribution data, and the Mann–Whitney *U* rank sum test will be used for non-normal distribution data. The comparison of count data between the two groups will be performed by *χ*^2^ test or Fisher’s exact test. An independent statistics expert will perform statistical analysis in a blind manner. SPSS for windows version 25.0 (SPSS Inc., Chicago, IL, USA) will be used for statistical analysis. The statistical level of significance will be set at *P* < 0.05.

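### Three unranked primary outcomes at two visits, each tested at P < 0.05, leave the trial's success criterion and its false-positive rate undefined

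*Protocol article*

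**What the plan says.** - **Outcomes.** The Outcome section states: "The primary outcome indicators are healthy behaviors, readmission rate, and anxiety level". The abstract lists the same three. The Objectives section gives them one shared aim: "explore whether recording positive events will promote or maintain healthy behaviors, reduce readmission rate, and improve anxiety of patients after PCI". No outcome is placed above the others.
- **Visits.** Under Primary outcome measure, the text on healthy behaviors (HPLP II) says "It will be checked at visits 1, 8, and 9", and the text on anxiety (SAS) says "The anxiety score will be measured at visits 1, 8, and 9". For readmission it says "The readmission information will be collected at visits 8 and 9", but also "The readmission will be followed up by telephone for 3 months", without saying which three months are meant. Table 1 places visit 8 at week 12, the end of the intervention, and visit 9 at week 24. Neither is called primary.
- **Tests.** Statistical analysis gives a two-sample t-test or Mann–Whitney test for measurement data and a chi-squared or Fisher test for counts. No model combines the visits. The only error rule is "The statistical level of significance will be set at" P < 0.05.
- **Sample size.** The calculation uses the "formula of sample size estimation based on the comparison of the mean of two independent samples", with two-sided alpha 0.05, power 0.8, σ = 12.68 and δ = 10.39. It names neither the outcome nor the visit.

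**The concern.** A trial with several primary outcomes needs to say what counts as success. Either one outcome at one visit decides, or all must succeed, or any one suffices with the error shared among them. This protocol makes none of these choices. Followed as written, it would allow any of up to six between-group results to be presented as a positive primary finding at the full 0.05 level, with the choice made after the data are seen. The sample size, meanwhile, is built for a single comparison at 0.05. What is at stake is whether a claimed primary effect carries the error rate that a reader would assume from P < 0.05.

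**Working it through.** **Inputs from the protocol article:** three primary outcomes (Outcome); two post-baseline visits (Table 1, Primary outcome measure); P < 0.05 (Statistical analysis); σ = 12.68, δ = 10.39, two-sided alpha 0.05, power 0.8, 25 per group, 20% loss, total 80 (Sample size calculation). **Assumed, because the documents give no values:** correlations between outcomes and between visits, and readmission rates.

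**1. The plan's own figure.** 2 × [(1.96 + 0.842) × 12.68/10.39]² = 23.39. Adding Z²/4 = 0.96 gives 24.35, so 25, as stated. (Adding a full Z², as the formula is printed, gives 27.23, so 28. That is a separate matter.) It is one comparison at one alpha. With 80 enrolled and 20% loss, 80 × 0.8/2 = 32 per arm are evaluable.

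**2. Independent tests, significance in either direction.**
- Three tests at one visit: 1 − 0.95³ = 14.3%.
- Six tests over both visits: 1 − 0.95⁶ = 26.5%.

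**3. Independent tests, false improvement only** (0.025 per test).
- Three tests: 1 − 0.975³ = 7.3%.
- Six tests: 1 − 0.975⁶ = 14.1%.
- A single test: 2.5%.

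**4. Correlated tests, all at full size.** Simulated normal statistics (1,000,000 draws), with assumed correlation 0 to 0.5 between outcomes and 0.5 to 0.8 between visits:

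| | Three tests | Six tests |
|---|---|---|
| Either direction | 12.5–14.3% | 19–25% |
| False improvement | 6–7% | 10–13% |

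**5. Conservative readmission test.** At 32 per arm, Fisher's exact test at nominal 0.05 has a true size of 0.2%, 1.1% and 2.4% for assumed readmission rates of 5%, 10% and 20%. Where expected counts allow chi-squared, the size at 20% is 4.6%, so the conservatism matters mainly when readmission is rare. With correlation 0.2 to 0.6 between the two scales and 0.5 to 0.8 between visits, the scales alone give 9–10% at one visit and 13–17% over two. Readmission is then added as independent at its Fisher size:
- Low end: 1 − (1 − 0.088)(1 − 0.0019) = 9.0% and 1 − (1 − 0.135)(1 − 0.0019)² = 13.8%.
- High end: 1 − (1 − 0.097)(1 − 0.0243) = 11.9% and 1 − (1 − 0.172)(1 − 0.0243)² = 21.2%.

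Steps 4 and 5 together give roughly 9–14% for three tests and 14–25% for six.

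**6. Cost of control.** The standardized difference is 10.39/12.68 = 0.819. Power by the noncentral t distribution at 32 per arm:
- alpha 0.05: 89.7%.
- alpha 0.05/3 = 0.0167: 79.0% (81% by the normal approximation, which gives n = 32 per arm).
- alpha 0.05/6 = 0.0083: 70.8%. The normal approximation needs 37 per arm, 47 with 20% loss, 94 in total.

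Three outcomes at one visit therefore fit within the planned 80, and six tests do not.

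**7. Readmission power.** For an assumed 20% versus 10% at 32 per arm, Fisher's test has about 11% power at 0.05 and about 5% at 0.0167.

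**The case against.** Several objections have force.

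- A reader might infer that the error rate simply is 14% to 26%. The documents do not support that. Those are independence values, so in effect ceilings, and the rate falls when outcomes and visits are positively correlated or readmission is rare.
- A reader might apply those figures to a false claim that an outcome improved. They count both directions. For improvement alone the ceilings are 7.3% and 14.1%, and the comparator is 2.5%, not 5%.
- A reader might infer that six tests are planned. The protocol fixes when outcomes are measured, not which visits are tested, and describes the readmission window only as three months.
- A reader might infer that any one significant outcome counts as success. The objective joins the three with *and*. If all three had to succeed at one visit, alpha would not be inflated. But no such rule is stated. Under it, power could not exceed that of the weakest outcome, about 11% if readmission is 20% versus 10%.
- The adjustment method is commonly left to a statistical analysis plan, which is not shown, so its absence alone would not be a finding.
- The objectives use exploratory wording, and larger trials are foreseen. However, the abstract also says that the study will verify the effects, so this only softens the point.

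These objections narrow the numbers. They do not supply a deciding outcome or visit. The protocol itself chose three co-equal primaries, simple tests and one significance level.

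**Conclusion.** The point holds in a limited form. The protocol fixes three unranked primary outcomes and two candidate visits at P < 0.05, with no success rule, and sizes the trial for one unnamed mean. The inflation is conditional on any one significant result counting as success. On that condition, the chance of at least one false significant primary result is up to about 14% (three tests) or 26% (six tests), and more plausibly 9–14% or 14–25% under the assumed correlations and readmission rates. The chance of a false improvement is at most about 7% or 14%, against 2.5%. If instead all three must succeed, the problem is power rather than alpha. Under either reading the criterion for a positive trial is undefined, and this should be settled before unblinding.

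**What to change.** Before unblinding, amend the protocol and the registry entry as follows.

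1. Name one primary visit, for example visit 8 at the end of the intervention, and make the other visit secondary. State which three-month window defines readmission.
2. Either name one primary outcome, namely the one behind σ = 12.68 and δ = 10.39, which the protocol should identify, or keep all three and test them at that visit with Holm at an overall two-sided 0.05 (steps 0.0167, 0.025, 0.05).
3. Report everything else with confidence intervals and no confirmatory claim.

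**Cost.** The change is one of wording and needs no extra patients. A single primary outcome costs no power for that outcome. Holm over three outcomes lowers power for the mean in the sample size calculation from about 90% to about 79% at its strictest step, with 32 evaluable per arm. This does not carry over to readmission, for which the trial has little power at either level under the assumed rates. Nor should baseline adjustment be credited with recovering the loss: the documents give no baseline correlation, and readmission has no baseline value.
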